#### **4.8 Statistical Analysis**

Individuals will be identified through a number to maintain data confidentiality, and all collected information will be typed into the Microsoft Office Excel® spreadsheet which will be stored on the institutional Google Drive®. Only the responsible researchers will have access to the data. After tabulation, the database will be exported to the SPSS v18.0 software to perform the statistical analysis. Descriptive data analysis will be performed according to the characteristics of each variable: mean and standard deviation or median and interquartile range for quantitative variables, and frequency and percentage for categorical variables.

Intent-to-treat (ITT) analyses will be performed for all outcomes. Primary and secondary outcomes will be analyzed using generalized linear mixed models (GLMM) with group, time, and their interaction as fixed effects, and random intercepts by participants. Age, sex, disease duration, and LEED will be included as baseline covariates in all models. Weekly laxative use will be included as a time-varying covariate to adjust for its potential confounding effect on bowel movement frequency. Missing data will be handled through the likelihood-based estimation inherent to GLMM, which provides valid estimates under the missing at random (MAR) assumption. Sensitivity analyses will be conducted to assess the robustness of results to potential departures from the MAR assumption.

Regarding the microbiota, alpha diversity ( $\alpha$ -diversity) will be evaluated by the Shannon index and statistical significance will be verified by linear modeling for mixed effects. Beta diversity ( $\beta$ -diversity) will be analyzed using Principal Component Analysis (PCA), Principal Coordinate Analysis (PCoA), and Non-metric Multidimensional Scaling (NMDS), all based on Aitchison (Aitchison, 1982) and Jaccard (Jaccard, 1908) distances. Statistical significance and the proportion of explained variance will be assessed using Permutational Multivariate Analysis of Variance (PERMANOVA) (Anderson, 2014) and linear models for mixed effects.

Differential abundance analyses will be performed using the Microbiome Multivariable Association with Linear Models 2 (Maaslin2) algorithm (Mallick et al., 2021). For multiple testing correction, the Benjamini-Hochberg (BH) method (Benjamini; Hochberg, 1995) will be applied to control the False Discovery Rate (FDR), as well as a mixed directional FDR control (mdFDR) will be used, with the application of the Family-Wise Error Rate control procedure by the Holm method (Holm, 1979), considering a significance level ( $\alpha$ ) of 0.05.

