#### **4.4 Primary Outcome**

The primary outcome of the study is the frequency of bowel movements per week, which will be assessed through the bowel movement diary.

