#### **4.5 Sample Size**

A sample size of 48 subjects (24 for each group) was calculated to test whether there is a minimum difference of 1 bowel movement/week between the mean bowel movements per week of the intervention and control groups at the last time point (week 12) of the repeated measures study (with the addition of 10% for possible losses and refusals, this number should be 54, 27 for each group). The calculation considered 80% power, a significance level of 5%, a standard deviation of 1.15 and 1.21 bowel movements/week for the intervention and control groups, respectively (Rusch et al., 2024). As well as 90% retention at time points 2 and a permutable correlation matrix with a correlation of 0.5. This calculation was performed using the PSS Health online tool (Borges et al., 2020).

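### Section 4.8 leaves the baseline value of the outcome out of the adjustment, forgoing a variance reduction of about a quarter at the plan's own correlation

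*Protocol*

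**What the plan says.** Section 4.4 sets the primary endpoint: "The primary outcome of the study is the frequency of bowel movements per week, which will be assessed through the bowel movement diary". Section 4.5 sizes the trial for a difference of 1 movement/week between the arm means in week 12, with "a standard deviation of 1.15 and 1.21 bowel movements/week for the intervention and control groups, respectively". It adds: "As well as 90% retention at time points 2 and a permutable correlation matrix with a correlation of 0.5".

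Section 4.8 prescribes one mixed model for primary and secondary outcomes, "with group, time, and their interaction as fixed effects, and random intercepts by participants". It then fixes the adjusters: "Age, sex, disease duration, and LEED will be included as baseline covariates in all models" (LEED is evidently the levodopa equivalent dose, LEDD, of section 4.7.6). Weekly laxative use is added as a time-varying covariate. The baseline value of the outcome is not on the list. The section does not say whether baseline is a level of time in the bowel-movement model, or which contrast is primary.

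Under section 4.7.4, nutritional status is measured only at baseline and D90. For those outcomes baseline has to be a level of time, or there is no group-by-time term to fit.

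**The concern.** The protocol assumes a correlation of 0.5 between repeated measurements when it sizes the trial, but its list of adjusters omits the earlier measurement of the same outcome.

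Putting baseline in as another response row does not supply the adjustment. With group, time and their interaction all free, each arm has its own baseline mean. The D90 group difference then draws nothing from baseline when data are complete, and the interaction is a plain difference in change scores. Neither contrast uses the fact that randomization makes the two arms' expected baseline means equal.

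At stake is precision on the primary outcome of a 54-person trial, and on the other outcomes with a baseline value under the same model: CSS, diet scores, nutritional status and MDS-UPDRS.

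**Working it through.** **Inputs (section 4.5).** Difference 1 movement/week; SDs 1.15 and 1.21; exchangeable correlation ρ = 0.5; 90% retention at the second time point; 80% power; 5% level, taken as two-sided because sidedness is not stated. A random intercept with a normal outcome implies the same exchangeable structure.

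**Step 1: reproduce the plan's sample size.** Sum of variances: 1.15² + 1.21² = 1.3225 + 1.4641 = 2.7866. With (1.960 + 0.842)² = 7.849, complete data need 7.849 × 2.7866 = 21.87 per arm. With 90% retention, the D90 variance factor in the free-means model is ρ² + (1 − ρ²)/0.9 = 0.25 + 0.75/0.9 = 1.0833. So n = 21.87 × 1.0833 = 23.69, or 24 per arm and 48 in total; 48/0.9 = 53.3, or 54. The stated figures are reproduced, with no credit taken for baseline adjustment.

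**Step 2: variance factors at ρ = 0.5.**

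| Contrast | Complete data | 90% retention at D90 |
|---|---|---|
| D90 difference, free baseline means | 1.00 | 1.0833 |
| Difference in change, 2(1 − ρ) | 1.00 | 1 + 1.0833 − 2(0.5) = 1.0833 |
| Baseline-adjusted or common baseline mean, 1 − ρ² | 0.75 | 0.75/0.9 = 0.8333 |

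The reduction is 1 − 0.75 = 25% with complete data and 1 − 0.8333/1.0833 = 23% with retention. The ratio 1.0833/0.8333 = 1.30 is equivalent to 30% more participants. In the planning formula, n per arm falls from 23.69 (24) to 21.87 × 0.8333 = 18.23 (19).

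**Step 3: power for 1 movement/week with 90% retention.** Standard error = √(2.7866 × factor / n).

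| n per arm | Factor | SE | Noncentral t, 2n − 2 df | Normal (z) formula |
|---|---|---|---|---|
| 24 | 1.0833 | 0.355 | 78.8% | 80.5% |
| 24 | 0.8333 | 0.311 | 88.2% | 89.5% |
| 27 | 1.0833 | 0.334 | 83.5% | 84.9% |
| 27 | 0.8333 | 0.293 | 91.7% | 92.6% |

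**Step 4: other correlations (assumed, complete data).**

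| ρ | D90 difference | Difference in change | Adjusted | Reduction against the better unadjusted contrast |
|---|---|---|---|---|
| 0.3 | 1.00 | 1.40 | 0.91 | 9% |
| 0.5 | 1.00 | 1.00 | 0.75 | 25% |
| 0.7 | 1.00 | 0.60 | 0.51 | 1 − 0.51/0.60 = 15% |

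The adjusted analysis has the smallest variance in all three rows.

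**Step 5: is a baseline value of the primary outcome available?** Section 4.6 places randomization after the baseline assessment, with D0 within 7 days after randomization. Section 4.7.1 has the diary filled in during the study period and states no window before randomization. The interval just before D0 is therefore post-randomization and may be shorter than a week.

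**The case against.** The strongest reply is that nothing in the plan is invalid. The sample size was computed without baseline adjustment, so the planned model delivers roughly the 80% it promises, and randomization keeps both unadjusted contrasts unbiased. That stands. A reader might infer that the trial is underpowered, or that chance baseline imbalance under simple randomization biases the result; the documents support neither. Chance imbalance adds noise, which the variance factors above already count.

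A second reply is that section 4.8 may already use baseline, through the interaction. For outcomes measured only at baseline and D90 it must, and for bowel movements the protocol leaves this open. So it would be too strong to say that the plan ignores baseline. But a change contrast with free baseline means still has factor 1.00 at ρ = 0.5, so the loss is the same.

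Third, such detail could sit in a separate analysis plan. That covers the choice of contrast, but not a covariate list that the protocol itself fixes for all models.

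Fourth, a quarter is the most favourable figure among the correlations tried when the comparison is with the better unadjusted contrast. The calculation also ignores variance explained by the listed covariates and laxative use, and section 4.8 names no distribution; a count model would shift the numbers. These limits stand.

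**Conclusion.** The point holds as a recommendation on efficiency. At the plan's own correlation, the model in section 4.8 forgoes a reduction of about a quarter of the variance (23% with 90% retention), whichever of the two contrasts is tested. By noncentral t, power would go from about 79% to 88% at 24 per arm and from about 84% to 92% at 27 per arm. Against the better unadjusted contrast, the reduction is about 9% at an assumed correlation of 0.3 and 15% at 0.7.

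The figures rest on a normally distributed outcome, equal correlation between time points, the section 4.5 SDs, a baseline value that correlates with the outcome as assumed there, and no variance explained by the listed covariates, for which the documents give no figure. The stated 48 (54 with losses) remains valid.

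**What to change.** In section 4.8, for every outcome measured at baseline, choose one of two forms:

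- keep baseline as a response and constrain the arms to a common baseline mean, with no group effect at baseline; or
- remove baseline from the response, model the later times, and enter baseline as a covariate.

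Do not do both, because that would use baseline twice. For outcomes measured only at baseline and D90, the second form reduces to ANCOVA with one row per participant, so the time, interaction and random-intercept terms drop out.

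For the diary outcome, define in sections 4.6 and 4.7.1 a baseline bowel-movement frequency that refers to the period before randomization, for example one recorded or reported at the baseline assessment. Do not use the interval between randomization and D0.

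The cost is a sentence or two in section 4.8 and the definition of that baseline value; no more participants are needed. The downside is that a recalled frequency may correlate less with the later diary counts than a diary value would, and the gain would then move towards the lower-correlation end of the range.

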#### **4.9 Ethical aspects**

This project was elaborated in accordance with the Guidelines and regulatory standards for research involving human beings (Resolution 466/12) and will be submitted to the Research Ethics Committee (CEP) of HCPA. The researchers declare that they know and comply with the requirements of the General Data Protection Law (Law N° 13.709, of August 14, 2018) regarding the treatment of personal data and sensitive personal data that will be used for the execution of this research project. The potential risks and benefits of the study are discriminated in the IC (APPENDIX B). The consent process will take place through the reading and understanding of the term, with subsequent signing by the individual who wishes to participate and the researcher. Two copies will be provided, one for the participant and one for the researcher. All collected data will be stored in a database within the institutional Google Drive® (@[hcpa.edu.br](mailto:hcpa.edu.br)) of the principal investigator. This data can only be accessed by the researchers cited here as the research team. Whenever possible, data will be anonymized, especially during statistical analysis. After the data collection period, participants in the control group will receive, if benefit is demonstrated, the nutritional guidelines that make up the nutritional intervention. All participants will receive feedback, if they wish, regarding the questionnaires applied.

## 5. BUDGET

| Materials                                                                                           | Quantity | Unit cost    | TOTAL                |
|-----------------------------------------------------------------------------------------------------|----------|--------------|----------------------|
| Anthropometric measuring tape                                                                       | 3        | R\$ 50,00    | R\$ 150,00           |
| CPC consultation room                                                                               | 120      | R\$ 7,55     | R\$ 906,00           |
| Publication support for a Qualis A journal                                                          | 1        | R\$ 3.000,00 | R\$ 3.000,00         |
| Double-sided printing copies                                                                        | 1000     | R\$ 0,26     | R\$ 260,00           |
| Article translation                                                                                 | 1        | R\$ 300,00   | R\$ 300,00           |
| ECG electrodes for use in BIA                                                                       | 432      | R\$ 0,48     | R\$ 207,36           |
| Drawer for sample storage in a cold chamber                                                         | 1        | R\$ 100,00   | R\$ 100,00           |
| Gut microbiota analysis                                                                      |          |              | R\$ 27.462,38 |
| DNA extraction kit - QIAamp PowerFecal Pro DNA Kit                                           | 2        | R\$ 2.885,02 | R\$ 5.770,04         |
| Enzyme for genomic library preparation - Phusion High-Fidelity PCR Master Mix with GC Buffer | 2        | R\$ 1.766,67 | R\$ 3.533,34         |
| Indexing kit for sequencing - Nextera XT Index Kit v2 Set A (96 indexes, 384 samples)        | 1        | R\$ 8.319,00 | R\$ 8.319,00         |
| Internal quality control for sequencing - PhiX CONTROL V3 KIT                                | 1        | R\$ 1.577,00 | R\$ 1.577,00         |
| Sequencing run cartridge - MiSeq™ i100 Series 25M Rgt Kit 600 cyc                            | 1        | R\$ 8.263,00 | R\$ 8.263,00         |
| TOTAL                                                                                        |          |              | R\$ 32.385,74 |

6. TIMELINE

| Project phases                                     | 2025/1 | 2025/2 | 2026/1 | 2026/2 | 2027/1 | 2027/2 | 2028/1 | 2028/2 |
|----------------------------------------------------|--------|--------|--------|--------|--------|--------|--------|--------|
| Project writing                                    | X      | X      |        |        |        |        |        |        |
| Submission to Brazil Platform                      |        | X      |        |        |        |        |        |        |
| Ethics Committee (CEP) approval                    |        | X      |        |        |        |        |        |        |
| ClinicalTrials.gov registration                    |        | X      |        |        |        |        |        |        |
| Data collection                                    |        | X      | X      | X      | X      |        |        |        |
| Nutritional intervention                           |        |        | X      | X      | X      |        |        |        |
| Statistical data analysis                          |        |        |        | X      | X      | X      |        |        |
| Scientific manuscript writing                      |        |        |        | X      |        | X      | X      |        |
| Publication and conference presentation of results |        |        |        | X      | X      | X      | X      | X      |
| PhD thesis defense                                 |        |        |        |        |        |        |        | X      |

## APPENDIX A - SPIRIT 2025 checklist

### SPIRIT 2025 checklist of items to address in a randomized trial protocol\*

| Section / Topic                                              | No | SPIRIT 2025 checklist item description                                                                                                                                                                            | Reported on page no. |
|--------------------------------------------------------------|----|-------------------------------------------------------------------------------------------------------------------------------------------------------------------------------------------------------------------|----------------------|
| Administrative information                            |    |                                                                                                                                                                                                                   |                      |
| Title and structured summary                                 | 1a | Title stating the trial design, population, and interventions, with identification as a protocol                                                                                                                  | 1                    |
|                                                              | 1b | Structured summary of trial design and methods, including items from the World Health Organization Trial Registration Data Set                                                                                    | 4                    |
| Protocol version                                             | 2  | Version date and identifier                                                                                                                                                                                       |                      |
| Roles and responsibilities                                   | 3a | Names, affiliations, and roles of protocol contributors                                                                                                                                                           | 3                    |
|                                                              | 3b | Name and contact information for the trial sponsor                                                                                                                                                                | -                    |
|                                                              | 3c | Role of trial sponsor and funders in design, conduct, analysis, and reporting of trial; including any authority over these activities                                                                             | -                    |
|                                                              | 3d | Composition, roles, and responsibilities of the coordinating site, steering committee, endpoint adjudication committee, data management team, and other individuals or groups overseeing the trial, if applicable | -                    |
| Open science                                          |    |                                                                                                                                                                                                                   |                      |
| Trial registration                                           | 4  | Name of trial registry, identifying number (with URL), and date of registration. If not yet registered, name of intended registry                                                                                 |                      |
| Protocol and statistical analysis plan                       | 5  | Where the trial protocol and statistical analysis plan can be accessed                                                                                                                                            |                      |
| Data sharing                                                 | 6  | Where and how the individual de-identified participant data (including data dictionary), statistical code, and any other materials will be accessible                                                             |                      |
| Funding and conflicts of interest                            | 7a | Sources of funding and other support (e.g., supply of drugs)                                                                                                                                                      |                      |
|                                                              | 7b | Financial and other conflicts of interest for principal investigators and steering committee members                                                                                                              |                      |
| Dissemination policy                                         | 8  | Plans to communicate trial results to participants, healthcare professionals, the public, and other relevant groups (e.g., reporting in trial registry, plain language summary, publication)                      |                      |
| Introduction                                          |    |                                                                                                                                                                                                                   |                      |
| Background and rationale                                     | 9a | Scientific background and rationale, including summary of relevant studies (published and unpublished) examining benefits and harms for each intervention                                                         | 8 -10                |
|                                                              | 9b | Explanation for choice of comparator                                                                                                                                                                              | 16                   |
| Objectives                                                   | 10 | Specific objectives related to benefits and harms                                                                                                                                                                 | 12                   |
| Methods: Patient and public involvement, trial design |    |                                                                                                                                                                                                                   |                      |
| Patient and public involvement                               | 11 | Details of, or plans for, patient or public involvement in the design, conduct, and reporting of the trial                                                                                                        | 35                   |
| Trial design                                                 | 12 | Description of trial design including type of trial (e.g., parallel group, crossover), allocation ratio, and framework (e.g., superiority, equivalence, non-inferiority, exploratory)                             | 12                   |

|                                                           |     |                                                                                                                                                                                                                                                                                                                             |             |
|-----------------------------------------------------------|-----|-----------------------------------------------------------------------------------------------------------------------------------------------------------------------------------------------------------------------------------------------------------------------------------------------------------------------------|-------------|
| Methods: Participants, interventions, and outcomes |     |                                                                                                                                                                                                                                                                                                                             |             |
| Trial setting                                             | 13  | Settings (e.g., community, hospital) and locations (e.g., countries, sites) where the trial will be conducted                                                                                                                                                                                                               | 12          |
| Eligibility criteria                                      | 14a | Eligibility criteria for participants                                                                                                                                                                                                                                                                                       | 13          |
|                                                           | 14b | If applicable, eligibility criteria for sites and for individuals who will deliver the interventions (e.g., surgeons, physiotherapists)                                                                                                                                                                                     | -           |
| Intervention and comparator                               | 15a | Intervention and comparator with sufficient details to allow replication including how, when, and by whom they will be administered. If relevant, where additional materials describing the intervention and comparator (e.g., intervention manual) can be accessed                                                         | 15 - 18     |
|                                                           | 15b | Criteria for discontinuing or modifying allocated intervention/comparator for a trial participant (e.g., drug dose change in response to harms, participant request, or improving/worsening disease)                                                                                                                        | -           |
|                                                           | 15c | Strategies to improve adherence to intervention/comparator protocols, if applicable, and any procedures for monitoring adherence (e.g., drug tablet return, sessions attended)                                                                                                                                              | 22          |
|                                                           | 15d | Concomitant care that is permitted or prohibited during the trial                                                                                                                                                                                                                                                           | 13          |
| Outcomes                                                  | 16  | Primary and secondary outcomes, including the specific measurement variable (e.g., systolic blood pressure), analysis metric (e.g., change from baseline, final value, time to event), method of aggregation (e.g., median, proportion), and time point for each outcome                                                    | 14; 18 - 25 |
| Harms                                                     | 17  | How harms are defined and will be assessed (e.g., systematically, non-systematically)                                                                                                                                                                                                                                       | -           |
| Participant timeline                                      | 18  | Time schedule of enrollment, interventions (including any run-ins and washouts), assessments, and visits for participants. A schematic diagram is highly recommended (see Figure)                                                                                                                                           | 15          |
| Sample size                                               | 19  | How sample size was determined, including all assumptions supporting the sample size calculation                                                                                                                                                                                                                            | 14          |
| Recruitment                                               | 20  | Strategies for achieving adequate participant enrollment to reach target sample size                                                                                                                                                                                                                                        | 12          |
| Methods: Assignment of interventions               |     |                                                                                                                                                                                                                                                                                                                             |             |
| Randomization:                                            |     |                                                                                                                                                                                                                                                                                                                             |             |
| Sequence generation                                       | 21a | Who will generate the random allocation sequence and the method used                                                                                                                                                                                                                                                        | 14          |
|                                                           | 21b | Type of randomization (simple or restricted) and details of any factors for stratification. To reduce predictability of a random sequence, other details of any planned restriction (e.g., blocking) should be provided in a separate document that is unavailable to those who enroll participants or assign interventions | 14          |
| Allocation concealment mechanism                          | 22  | Mechanism used to implement the random allocation sequence (e.g., central computer/telephone; sequentially numbered, opaque, sealed containers), describing any steps to conceal the sequence until interventions are assigned                                                                                              | 14          |
| Implementation                                            | 23  | Whether the personnel who will enroll and those who will assign participants to the interventions will have access to the random allocation sequence                                                                                                                                                                        | 14          |
| Blinding                                                  | 24a | Who will be blinded after assignment to interventions (e.g., participants, care providers, outcome assessors, data analysts)                                                                                                                                                                                                | 14          |

|                                                           |     |                                                                                                                                                                                                                                                                                                                                                                                        |         |
|-----------------------------------------------------------|-----|----------------------------------------------------------------------------------------------------------------------------------------------------------------------------------------------------------------------------------------------------------------------------------------------------------------------------------------------------------------------------------------|---------|
|                                                           | 24b | If blinded, how blinding will be achieved and description of the similarity of interventions                                                                                                                                                                                                                                                                                           | 14      |
|                                                           | 24c | If blinded, circumstances under which unblinding is permissible, and procedure for revealing a participant's allocated intervention during the trial                                                                                                                                                                                                                                   | -       |
| Methods: Data collection, management, and analysis |     |                                                                                                                                                                                                                                                                                                                                                                                        |         |
| Data collection methods                                   | 25a | Plans for assessment and collection of trial data, including any related processes to promote data quality (e.g., duplicate measurements, training of assessors) and a description of trial instruments (e.g., questionnaires, laboratory tests) along with their reliability and validity, if known. Reference to where data collection forms can be accessed, if not in the protocol | 18 - 25 |
|                                                           | 25b | Plans to promote participant retention and complete follow-up, including list of any outcome data to be collected for participants who discontinue or deviate from intervention protocols                                                                                                                                                                                              | 18      |
| Data management                                           | 26  | Plans for data entry, coding, security, and storage, including any related processes to promote data quality (e.g., double data entry; range checks for data values). Reference to where details of data management procedures can be accessed, if not in the protocol                                                                                                                 | 25      |
| Statistical methods                                       | 27a | Statistical methods used to compare groups for primary and secondary outcomes, including harms                                                                                                                                                                                                                                                                                         | 25 - 26 |
|                                                           | 27b | Definition of who will be included in each analysis (e.g., all randomized participants), and in which group                                                                                                                                                                                                                                                                            | 25 - 26 |
|                                                           | 27c | How missing data will be handled in the analysis                                                                                                                                                                                                                                                                                                                                       | 27      |
